# Effects of Functional Electrical Stimulation Combined With Usual Physiotherapy on Hand Pain and Function in Stroke: Protocol for a Double‐Blind Randomized Controlled Trial

**DOI:** 10.1002/hsr2.73276

**Published:** 2026-09-23

**Keywords:** functional electrical stimulation, hand function, hand pain, physiotherapy, stroke

## Abstract

**Background and Aims:**

Stroke is a leading cause of long‐term disability, often causing upper extremity paralysis that limits daily activities. Functional electrical stimulation (FES) has been shown to promote motor recovery by activating affected muscles, but its effectiveness when combined rigorously with usual physiotherapy treatment (UPT) remains underexplored. This trial aims to assess whether FES combined with UPT improves hand pain and function in stroke patients more than UPT with placebo FES.

**Methods:**

This prospective, randomized controlled trial will recruit 140 stroke patients, who will be randomly assigned to either the intervention group (*n* = 70) or the control group (*n* = 70). The intervention group will receive 30 min of FES applied to the wrist extensors combined with 30 min of UPT, while the control group will receive placebo FES along with the same UPT protocol, 3 days a week for 8 weeks. Outcomes will be measured at baseline, mid‐intervention (week 4), post‐intervention (week‐8), and after 12‐week follow‐up (week‐20). Primary outcomes will be hand pain, assessed with the Numerical Pain Rating Scale (NPRS), and upper extremity function, assessed with the Fugl‐Meyer Assessment–Upper Extremity (FMA‐UE). Secondary outcomes will include muscle tone, measured by the Modified Ashworth Scale (MAS), and manual dexterity, measured by the Box and Block Test (BBT).

**Results:**

All outcomes will be assessed at baseline, mid‐intervention, post‐intervention, and follow‐up to evaluate both short‐term and sustained effects. Comparative analyses will be conducted to determine the effectiveness of FES combined with UPT versus placebo FES with UPT in improving pain and functional outcomes in stroke.

**Conclusions:**

This trial will provide high‐quality evidence regarding the adjunctive role of FES in stroke rehabilitation. The findings are expected to support evidence‐based physiotherapy practice, enhance clinical decision‐making, and improve functional recovery and quality of life for individuals with stroke‐related upper extremity impairments.

**Trial Registration:** CTRI/2025/07/091676.

## Introduction

1

Globally, stroke is one of the most frequent causes of death and a primary cause of acquired adult disability [1]. Nearly 12 million new strokes occur annually worldwide. One out of every four people who are above 25 years old will have a stroke in their lives [2]. In Bangladesh, the prevalence of stroke is 1.04 per 1000 people, with males having a significantly higher rate, 1.58 times greater than females [3]. The functional and disability status of individuals post‐stroke varies according to their age, gender, and type, phases, and chronicity of stroke [4]. The upper extremity is one of the most commonly affected stroke areas, with impairments specifically predominant in the hand [5]. Upper extremity disability commonly occurs in about 50% of stroke cases [6, 7, 8]. Patients with stroke tend to experience poor hand performance because of the severity of motor loss, sensory loss, and lack of coordination. Patients with a Fugl‐Meyer upper‐extremity test score below 11 points 2 weeks after stroke have minimal chances of regaining any measurable hand dexterity, as well as a low probability of regaining upper‐extremity functional capacity [9, 10]. Immediate rehabilitation is strongly advised to support individuals who have experienced a stroke in diminishing residual functional disabilities and complications in post‐stroke. Rehabilitation helps to augment the quality of life by reducing functional disability and stroke complications that may mitigate the need and expense of long‐term care [11].

Pain after stroke can impair psychological well‐being, daily function, working abilities, and a person's quality of life [12, 13, 14]. The prevalence of post‐stroke pain ranges from 19% to 74%, influenced by pain classification systems, follow‐up duration, and assessment methods. Central pain can result from thalamic lesions, while peripheral pain can result from secondary deficits and abnormal muscle tone [15]. After a stroke, the upper extremities are the most commonly affected site of peripheral pain. However, hand pain is reported in 4.6% of the elderly stroke population [16, 17, 18]. Functional status of the upper extremity is a significant focus during rehabilitation for people with a stroke [19]. Over the last 10 years, the number of studies focusing on stroke rehabilitation of the upper extremity has increased rapidly [18]. Numerous studies have evaluated the effectiveness of physiotherapy interventions for stroke by comparing experimental treatments with standard or conventional therapy [18, 19, 20, 21]. A variety of therapeutic approaches have been used to improve upper‐extremity motor function following a stroke, including Functional Electrical Stimulation (FES) [9, 10, 18, 19, 20]. FES involves the use of electrical impulses that stimulate the nerves attached to paralysed muscles. It can be employed as an intervention during upper extremity rehabilitation because it stimulates the contraction of paralysed and weak muscles, enabling a person to perform movements and actions such as gripping a key, holding a toothbrush, and using utensils [20]. FES can be used to create movements or functions that resemble typical voluntary movements for the purposes for which those movements are intended [21, 22].

Despite the widespread use of FES in neurorehabilitation, current evidence regarding its effectiveness in reducing hand pain and improving function in people with stroke remains inconclusive. Several studies have reported improvements in motor performance following FES application; however, considerable variability in intervention protocols, outcome measures, and study populations limits the generalizability of the findings. Moreover, pain is a significant yet often underreported barrier to functional recovery and has not been adequately addressed in most of the FES‐focused trials. Notably, few randomized controlled trials (RCTs) have concurrently examined both pain and hand‐specific functional outcomes following FES in individuals with stroke [21]. Although recent literature encourages the use of FES in upper extremity stroke rehabilitation, its application, especially when combined with well‐structured standard care for post‐stroke hand impairments, remains limited and still unfamiliar in clinical settings. Previous studies have shown mixed results, often hindered by poor methodology, limited outcome measures, and a lack of long‐term follow‐up, leaving their optimal effectiveness uncertain when assessed with robust methodological standards [13, 18].

Therefore, this prospective, randomized controlled trial (RCT) is relevant and aims to complement and contribute to the existing scientific effort by maintaining a strong methodological rigor. The primary objective of this trial is to evaluate the effectiveness of FES‐integrated UPT in reducing hand pain and improving hand function in stroke patients. The secondary objectives are: (1) to evaluate sociodemographic factors such as age, gender, stroke type, and time since stroke that may affect post‐stroke pain and functional recovery; (2) to establish baseline compatibility between the experimental and control groups; (3) to assess changes and compare group differences across all outcome measures at mid and post‐intervention periods; and (4) to explore the long‐term benefits of FES‐integrated UPT in maintaining improvements during the follow‐up period. It is hypothesized that FES‐integrated UPT will result in significantly greater improvements in hand pain, function, muscle tone, and manual dexterity compared to placebo FES with UPT, with these improvements being more long‐lasting.

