#### Inclusion Criteria

2.6.1

Participants must meet all of the following to be eligible for the study: (1) Confirm diagnosis of unilateral ischemic stroke verified by CT or magnetic resonance imaging (MRI) by a neurologist [24]; (2) Age between 40 and 70 years; (3) Stable vital signs with normal levels of consciousness; (4) Brunnstrom recovery stage between 3 or less for the affected upper extremity function [25, 26]; (5) Presence of mild‐to‐moderate spasticity in the affected upper extremity, based on Modified Ashworth Scale (MAS) score of 1 to 2 in the wrist flexor muscles; (6) Stroke onset between 1 and 3 months before enrollment [27]; (7) Willingness and ability to provide informed consent to participate in the study.

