#### Exclusion Criteria

2.6.2

Participants will be excluded if they: (1) Have a previous history of stroke, including reversible ischemic or hemorrhagic stroke; (2) Exhibit severe cognitive impairments or significant speech and communication difficulties; (3) Have a diagnosis of any mental health disorders (e.g., schizophrenia); (4) Have an implanted cardiac pacemaker [28].

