### Outcome Measurements

2.8

The primary outcome measures will focus on hand pain and function, with hand pain measured using the Numeric Pain Rating Scale (NPRS) and hand function using the Fugl‐Meyer Assessment for Upper Extremity (FMA‐UE). Secondary outcomes will include muscle tone and manual dexterity, with muscle tone measured using the MAS and manual dexterity using the Box and Block Test (BBT). Spasticity will specifically be evaluated in the wrist flexors, finger flexors, and elbow flexors of the affected limb, as these muscle groups are commonly associated with post‐stroke upper extremity spasticity patterns. Individual participant sociodemographic information related to stroke will also be collected at baseline assessment. The primary and secondary outcomes will be measured at four time points: baseline, mid‐intervention (week 4), post‐intervention (week 8), and 12‐week follow‐up (week 20).

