### Data Analysis

2.13

All analyses will be conducted by an independent statistician using SPSS version 22 with anonymized, encrypted data. Data will be screened for completeness, missing values, and outliers prior to analysis. Normality will be assessed using the Kolmogorov–Smirnov and Shapiro–Wilk tests, along with measures of skewness and kurtosis, and visual inspection (histograms and *Q*–*Q* plots). Descriptive statistics will be presented as mean ± standard deviation for normally distributed variables, median (interquartile range) for non‐normally distributed variables, and frequency (percentage) for categorical variables. Baseline characteristics (e.g., age, BMI, disease duration) will be compared between the two groups to assess group equivalence. Given the two‐group design (intervention vs control) with four time points (baseline, mid‐intervention, post‐intervention, and follow‐up), a two‐way repeated‐measures ANOVA (group × time) will be used for normally distributed outcomes to evaluate main effects and interaction effects. For non‐normally distributed data, the Friedman test (within‐group) and Mann–Whitney *U* test (between‐group at each time point) will be applied, with appropriate post hoc analyses. Within‐group changes over time will be assessed using repeated‐measures ANOVA (or Friedman test), while between‐group differences at each time point will be examined using independent *t*‐tests (or Mann–Whitney *U* tests). When significant interactions are identified, post hoc pairwise comparisons with appropriate corrections (e.g., Bonferroni) will be performed. Effect sizes (e.g., partial eta squared or Cohen's *d*) and mean differences with 95% confidence intervals will be reported alongside p‐values. All tests will be two‐tailed, with statistical significance set at *p* < 0.05. An intention‐to‐treat (ITT) approach will be applied, and missing data will be handled using the last observation carried forward (LOCF) method. Additionally, change scores across all four time points will be calculated to support the interpretation of clinical relevance.

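### Secondary objective 1 names stroke type as a factor to evaluate, but only ischemic stroke is eligible; separately, the stated treatment comparison adjusts for none of the named factors.

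*Protocol article*

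**What the plan says.** The last paragraph of the Introduction lists four secondary objectives. The first is "to evaluate sociodemographic factors such as age, gender, stroke type, and time since stroke", as influences on pain and functional recovery after stroke.

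Eligibility is set in sections 2.6.1 and 2.6.2:
- The first inclusion criterion is "Confirm diagnosis of unilateral ischemic stroke verified by CT or magnetic resonance imaging (MRI) by a neurologist".
- The first exclusion criterion is "Have a previous history of stroke, including reversible ischemic or hemorrhagic stroke".
- Age and onset are bounded: "Age between 40 and 70 years" and "Stroke onset between 1 and 3 months before enrollment". Gender is not restricted.

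On data collection, section 2.8 states: "Individual participant sociodemographic information related to stroke will also be collected at baseline assessment".

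On analysis, section 2.13 specifies a group × time repeated-measures ANOVA that "will be used for normally distributed outcomes to evaluate main effects and interaction effects". It adds t-tests between groups at each time point, with Friedman and Mann–Whitney tests for non-normal data. The one use it gives to baseline characteristics is a between-group check of equivalence. It names no covariate.

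**The concern.** There are two separate matters.

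The first is a contradiction inside the protocol. An objective promises to evaluate a factor that the eligibility criteria hold constant. The final report would have to drop that part of a declared objective without comment, or explain afterwards why it could not be done.

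The second concerns the efficiency of the treatment comparison. The Introduction says that functional and disability status after stroke differs by age, gender and chronicity, among other things. Yet the group comparison stated in section 2.13 uses none of these, and the t-tests at each time point do not use the baseline score either. The result remains valid, but precision available from data taken at baseline is given up.

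**Working it through.** **1. Can each named factor be evaluated?** Setting the objective beside the eligibility criteria:

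| Factor in objective 1 | Values allowed by sections 2.6.1 and 2.6.2 | Estimable? |
|---|---|---|
| Age | 40 to 70 years | Yes |
| Gender | Unrestricted | Yes |
| Time since stroke | 1 to 3 months | Yes, over a narrow range |
| Stroke type | Ischemic only; no previous stroke of any kind | No |

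A design-matrix check on simulated data with 128 participants agrees. A model with intercept, group, age, gender and time since stroke has 5 columns and rank 5. Adding a stroke-type column that is the same for everyone gives 6 columns, still of rank 5. The added column has variance 0 and is indistinguishable from the intercept.

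**2. What can the trial say about the other three factors?** For a two-sided 5% test with 80% power, the smallest detectable correlation is about tanh[(1.960 + 0.842)/√(N − 3)]. At N = 128 this is tanh(2.802/11.18) = 0.245. At N = 140 it is 0.235. Exploratory evaluation is therefore feasible.

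**3. The plan's own sample size.** The inputs from section 2.3 are d = 0.5, two-tailed α = 0.05 and power 0.80. The noncentral t calculation gives 63.77, rounded up to 64 per group, or 128 in all. Power at 64 per group is 0.801. The stated figure reproduces and is not in dispute.

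**4. What adjustment would be worth.** If the covariates together explain a share R² of the outcome variance, the residual SD shrinks by √(1 − R²), so the effective standardised difference is d/√(1 − R²). The protocol gives no R², so the range below is assumed. Power is from the noncentral t-test at 64 per group, two-sided 0.05.

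| R² (assumed) | Effective d | Power |
|---|---|---|
| 0 | 0.500 | 80.1% |
| 0.05 | 0.5/√0.95 = 0.513 | 82.1% |
| 0.10 | 0.5/√0.90 = 0.527 | 84.1% |
| 0.20 | 0.5/√0.80 = 0.559 | 88.1% |

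Four covariates (baseline score, age, gender, time since stroke) reduce the residual degrees of freedom from 126 to 122. That lowers each power figure by about 0.02 percentage points, which is negligible.

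**The case against.** The strongest reply has four parts.

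*The objective is not impossible.* A reader might infer that secondary objective 1 as a whole cannot be met. The protocol does not support that. The list of factors is illustrative, three of the four vary, and step 2 shows that they can be studied. This objection stands, and the contradiction is confined to stroke type.

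*Silence is not prohibition.* A reader might also infer that, because section 2.13 gives no prognostic-factor model, the plan leaves objective 1 without an answer. This is a condensed journal article, and such a model could be in an analysis plan that is not shown. This stands too, so the missing model is not counted as a defect. It does not rescue stroke type, because eligibility, not analysis, removes the variation. Stroke type could be meant as ischemic subtype, but the article defines none, and section 2.6.2 itself uses the ischemic/hemorrhagic distinction.

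*An unadjusted comparison in a randomized trial is valid.* That is true, and the second matter is an improvement in precision, not the correction of an error. The unadjusted comparison is, however, what section 2.13 states, so the remark does not rest on an omission.

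*The power figures are soft.* They rest on an assumed R² and on a comparison at one time point, as in section 2.3. The ANOVA in section 2.13 treats baseline as one of its time levels and so already makes some use of it. The restricted age and onset ranges could keep the share explained by those factors small. This stands as a limit on the size of the gain, not on its direction.

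**Conclusion.** The point holds in two limited parts.

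First, stroke type in objective 1 contradicts the ischemic-only eligibility. This follows from the text alone and needs no assumption beyond the ordinary ischemic/hemorrhagic meaning of the term. The contradiction changes no sample-size figure.

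Second, the stated group comparison leaves out baseline information that the Introduction itself links to functional status. Adjusting for it would raise power at 64 per group from 80% to about 82%, 84% or 88% if the covariates explain 5%, 10% or 20% of outcome variance. That range is assumed.

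Neither part threatens the validity of the treatment comparison. Both are minor, and according to section 2.16 recruitment has not begun.

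**What to change.** - **Introduction, objective 1:** delete stroke type, or define it as a named ischemic subtype and record it at baseline.
- **Section 2.13:** for the continuous outcomes (NPRS, FMA-UE, BBT), estimate the between-group effect from a model adjusted for the baseline score of that outcome and for pre-specified age, gender and time since stroke. Report the coefficients of the three factors as exploratory, as the answer to objective 1.
- **Section 2.8:** list the three factors among the baseline data. The section speaks only of sociodemographic information in general. Section 2.13 gives age and disease duration as examples but does not mention gender.

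The cost is a wording change in the objective, a short revision of section 2.13, a little more analysis work and a few degrees of freedom. For these three outcomes the covariate model would take the place of the rank tests, so it is slightly more than an added sentence. The recruitment target stays at 140.

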### Sample Size Calculation

2.3

Sample size calculation is performed using G*Power software version 3.1.9.7 for a two‐tailed independent‐groups test comparing two group means. The effect size (Cohen's *d*) is set to 0.5 (medium effect) based on prior research in post‐stroke rehabilitation [23]. The α value is predetermined as 0.05, and the power (1–β) is 0.80 to limit the risk of Type II error. Based on these parameters, we will need 64 individuals per group, for a total of 128 participants. Finally, we plan to recruit 140 participants (70 per group), allowing for an anticipated dropout rate of approximately 10%.

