### Randomization and Blinding Procedures

2.5

Following consent, participants will be randomly assigned in a 1:1 ratio to either Group A or Group B using simple randomization performed through Excel's = RAND() function by an independent research assistant not involved in recruitment, treatment, or assessment. Allocation concealment will be ensured using sequentially numbered, opaque, sealed envelopes prepared by an independent assistant. This study will employ participants, and outcome assessors will be blinded to group allocation throughout the study period. Due to the nature of the intervention, treating physiotherapists administering FES cannot be blinded; however, they will not participate in outcome assessment or data analysis. Participants in both groups will receive identical treatment durations, therapist interactions, electrode placement procedures, and device preparation to maintain the credibility of blinding. Outcome assessments and statistical analyses will be conducted by independent personnel blinded to treatment allocation. Participants will also be instructed not to discuss their intervention experiences with assessors to minimize detection bias.

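### Secondary objective 2 aims to establish that the randomised groups are alike at baseline, which the planned comparison cannot show

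*Protocol article*

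**What the plan says.** The Introduction of the protocol article lists four secondary objectives. The second is "to establish baseline compatibility between the experimental and control groups".

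Section 2.13 (Data Analysis) carries this out. Baseline characteristics, with age, BMI and disease duration as examples, "will be compared between the two groups to assess group equivalence". That sentence names no test. The same section plans a group × time repeated-measures ANOVA, and adds that "between‐group differences at each time point will be examined using independent" t-tests or Mann–Whitney U tests. Baseline is one of the four time points. A general rule closes the matter: "All tests will be two‐tailed, with statistical significance set at" p < 0.05. The article states no equivalence margin, no equivalence test and no threshold for a relevant imbalance.

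Section 2.5 (Randomization and Blinding Procedures) describes "simple randomization performed through Excel's = RAND() function by an independent research assistant", with concealment by sequentially numbered, opaque, sealed envelopes. Section 2.3 (Sample Size Calculation) gives 64 per group, raised to 70 per group for dropout.

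**The concern.** The objective asks for a positive conclusion, that the groups are alike. A test of difference cannot supply it, because a non-significant result is also what an imprecise comparison gives. Nor is there a real hypothesis to test. When allocation is random and concealed, both groups come from one population, and any baseline difference is a chance difference.

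At stake is the reporting, and the reassurance that readers take from it. Followed as written, the plan could present equivalence as an established finding when the data rule out only large imbalances. In the other direction, a chance p-value below 0.05 on one variable could be read as incompatibility of groups that were properly randomised. Neither result says how far a realised imbalance in a prognostic variable has moved the outcome comparison, which is the useful question.

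**Working it through.** **Inputs.** 70 per group, design effect d = 0.5, two-tailed comparison of two independent means, power 0.80 and alpha 0.05 (section 2.3). Significance rule p < 0.05, two-tailed, and three example baseline variables (section 2.13). Concealed simple randomisation (section 2.5).

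**1. The plan's own sample size.** For d = 0.5, two-sided alpha 0.05 and power 0.80, the noncentral-t calculation gives 63.77, rounded up to 64 per group, with power 0.801. The stated 64 is reproduced and is not in dispute.

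**2. Largest observed imbalance that stays non-significant.** For a two-sample t-test with n per arm, the threshold in SD units is t(0.975, 2n − 2) × √(2/n). With n = 70: 1.977 × √(2/70) = 1.977 × 0.169 = 0.334. As a share of the design effect: 0.334 / 0.5 = 0.67, or two thirds. Two points either side of the threshold:

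| Observed imbalance | t = imbalance / 0.169 | p (two-sided) | Flagged? |
|---|---|---|---|
| 0.3 SD | 1.77 | about 0.08 | No |
| 0.4 SD | 2.37 | about 0.02 | Yes |

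Simple randomisation need not give exactly 70 and 70, but this matters little. With 60 and 80 the threshold is 1.977 × √(1/60 + 1/80) = 1.977 × 0.171 = 0.34 SD.

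**3. False alarms under sound randomisation.** The null hypothesis is then true by design, so each test has a 5% chance of p < 0.05. For k independent tests the chance of at least one is 1 − 0.95^k:

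| k | Chance of at least one p < 0.05 |
|---|---|
| 3 (the named examples) | 1 − 0.857 = 14% |
| 7 (assumed) | 30% |
| 10 (assumed) | 1 − 0.599 = 40% |

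The article does not give the full number of baseline variables, hence the range. Correlation between the variables would change these figures.

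**4. Could the objective be met properly?** It would need a margin, and none is stated. For two one-sided tests at 0.05 with a true difference of zero and 80% power, n per arm = 2 × ((1.645 + 1.282) / M)², with M in SD units:

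| Assumed margin M | n per arm | Power with 70 per arm |
|---|---|---|
| 0.20 SD | 429 | about 0 |
| 0.30 SD | 191 | 0.10 |
| 0.50 SD | 69 | 0.81 |

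Of these margins, 70 per arm is enough only for 0.5 SD, and that equals the whole effect the trial is sized to detect.

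**The case against.** The strongest reply is that the article never says baseline characteristics will be tested. The sentence follows the one on descriptive statistics, says only that they will be compared, and the per-time-point tests plainly concern the repeated outcomes, not age or BMI. This stands in part: the test is an inference from the section-wide significance rule and from the absence of any other between-group method. It does not rescue the objective, because a descriptive table cannot establish equivalence either.

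Second, nothing in the plan depends on the baseline comparison, and the main analysis does not ignore baseline. That also stands. A reader might infer that the trial would declare its randomisation failed, or that a baseline imbalance in NPRS or FMA-UE goes wholly uncorrected. The article supports neither. No action is tied to the result, and the group × time interaction compares changes from baseline, so it partly takes baseline outcome values into account. The separate t-tests or Mann–Whitney tests at each time point do not.

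Third, a reader might measure the fault by the test's power, noting that with 70 per arm a true difference of 0.3 SD is missed 58% of the time and one of 0.4 SD 35% of the time. The arithmetic is correct but does not apply here. Under the concealed randomisation described there is no true difference to miss, only a realised one. An observed 0.4 SD is always flagged and an observed 0.3 SD never is. Realised gaps of that size are also uncommon: about 8% per variable for 0.3 SD or more, and 2% for 0.4 SD or more.

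Finally, the choice of covariates is often left to a statistical analysis plan, which is not shown. The absence of a covariate list is therefore not the fault raised here. The fault is the stated aim.

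**Conclusion.** The concern holds as a minor point about inference. Secondary objective 2 and the equivalence phrase in section 2.13 set an aim that the planned comparison cannot meet. If tests of difference are used, observed imbalances up to about 0.33 SD pass as equivalent, while sound randomisation still yields at least one significant result with probability of about 14% (three variables) to 40% (ten).

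These figures assume t-tests on roughly normal variables, about 70 per arm, and independent tests. The count of ten and the equivalence margins are assumptions, not figures from the article. The fault does not change the sample size and does not of itself bias the primary comparison.

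**What to change.** - Delete secondary objective 2 from the Introduction and the words on group equivalence from section 2.13.
- Present baseline characteristics by arm descriptively, without p-values and without a conclusion about equivalence. Confine the between-group comparisons to the post-baseline time points.
- In those comparisons, adjust for the baseline value of the outcome (NPRS or FMA-UE) and for age and time since stroke, fixed in advance and applied whatever the observed balance. All of these are already to be collected.

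**Cost.** One objective and a set of tests are dropped. The adjustment is more than a change of wording: t-tests and Mann–Whitney tests cannot carry covariates, so a covariate-adjusted model replaces the unadjusted tests at each time point, with a little more analysis work. The sample size and data collection are unchanged. Section 2.16 says that no participants have yet been recruited, so the change can be made before any data exist.
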